### **9.1.3 Safety analysis**

Safety analysis will be performed in the safety population. Regardless of the reason for the completion of the study, the data of all patients who received at least one IP/Placebo dose according to the assignments will be included in the safety analysis.

Adverse events will be coded using MedDRA dictionary. Incidences of TEAEs/SAEs will be calculated for assessment of AEs. Incidences of adverse events reported during the study will be presented as number of patients with AE in total and in each treatment group. Also, number of AEs per each severity category and per causal relationship with the study drug will be presented.

Incidences of adverse events will be compared between the IP and the Placebo group. The proportion of patients **with at least one adverse event** will be compared in the NeuroAiD II™ group and in the placebo group.

Vital Signs, Laboratory tests, Physical examination, ECG, Pregnancy test results will be tabulated by visits. Descriptive statistics by visit and for change from baseline will be summarized. Number of clinically significant (assessed by the Investigator) deviations in the results of haematology, blood chemistry and urine laboratory tests upon NeuroAiD II™/Placebo treatment completion

(Day 180±14) in the NeuroAiD II™ group and in the Placebo group compared to baseline will be tabulated.

No formal statistical testing is assumed for safety analysis.

## 9.2 Number of Subjects Planned to be Enrolled

The primary endpoint for the trial is change in complex attention score, determined using CNS-VS computer cognitive testing system, after 6 months of treatment compared to baseline in the group of patients receiving NeuroAiD II™ (MLC901), compared to the placebo group. Primary Analysis: the primary analysis will compare the mean change in the complex attention score, determined by CNS-VS testing, after 6 months of therapy after 6 months of treatment, compared to baseline, between the MLC901 group and the placebo group by analysis of variance in the ITT population.

In a study of Gualtieri (46-48), CNS-VS complex attention score was compared between patients who had recovered from mild brain injury/concussion (with loss of consciousness less than 20 minutes and/or transient post-traumatic amnesia (less than 24 hours) and normal patients. CNS-VS Complex Attention score was assessed at 100.41 in the subgroup on normal patients, as compared to an average of 92.8 in the mild brain injury/concussion subgroup (46,47,48). These results suggest that a difference in complex attention score in the range of 8-10 is clinically important and distinguish normal subjects from subjects with some level of post brain injury impairment.

The sample size for this study is estimated based upon a previous study in 78 patients evaluating the effect of MLC-901 (NeuroAiD II) versus placebo using CNS-VS as main efficacy assessment (21). Results obtained at 6 months for CNS-VS complex attention in (21) are displayed in the following table:

*Table 9.1. Complex Attention score: Mean (SD) (extract from the Supplementary Table 1 in (21))*

| Group          | MLC-901 (n=36) | Placebo (n=42) |
|----------------|----------------|----------------|
| Baseline       | 83.86 (22.06)  | 85.43 (16.52)  |
| After 6 months | 94.18 (15.29)  | 82.31 (21.56)  |

While the scores are very similar at baseline, there is a difference of about 12 points at 6 months between placebo and MLC-901 groups, in favor of the active treatment. Based upon these results, sample size for current study has been calculated in order to provide 80% power to detect a difference of 10 points in CNS-VS Complex Attention score change from baseline after 6 months (at a 2-sided alpha level 5%). The standard deviation used in this calculation for the parameter is estimated to be 20.

Study is powered to claim superiority of MLC901 over Placebo by primary endpoint for following statistical hypothesis:  $H_0: LSM_T \geq LSM_R$ ,  $H_1: LSM_T < LSM_R$ , where  $LSM_T$  is a Least Square Mean of Change from Baseline of Complex attention score after 6 months of treatment assessed by the mixed model repeated measures analysis in the MLC901 group and  $LSM_R$  is a Least Square Mean of Change from Baseline of Complex attention score after 6 months of treatment assessed by the mixed model repeated measures analysis in the Placebo group (lower score of Complex attention is better).

PASS 14 software (Scenario: two sample T-test assuming equal variance) was used to estimate the required sample size. Target power – 80%. Alpha – 0.05. Proportion of subjects in groups – 1:1.

Hypotheses: H0:  $MT \geq MR$ , H1:  $MT < MR$ , where MT is an arithmetical mean of change of Complex attention score after 6 months of treatment, compared to baseline, in the MLC901 group, and MR is an arithmetical mean of change from baseline of Complex attention score after 6 months of treatment in the placebo group (lower score of Complex attention is better).

An estimate of 20 was obtained from the BRAINS pilot study (21) for standard deviation of change in complex attention from baseline to 6 months, 128 subjects (64 per arm) are required to detect a clinically meaningful difference of -10 in the mean changes in complex attention between MLC901 and placebo arms with 80% power at a two-sided 5% significance level. Sensitivity analysis: 1) power is equal 29% if the mean difference of primary estimate is 5 and power is equal 99% if the mean difference of primary estimate is 20; 2) power is equal 15% if the standard deviation increases up to 30, so some uncertainty in the standard deviation estimate may cause insufficient actual power for comparison.

The sample size is increased to 182 randomized subjects (91 per arm) to allow for 30% dropouts. Considering very high screening failure rate up to 364 subjects can be screened.

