### **9.3 Level of Significance to be Used**

The two-sided significance level of 0.05 (5%) will be applied for all statistical tests.

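### Section 9.2 gives 15% power at an SD of 30, but at the design difference of 10 points the figure is about 46%; 15% needs the difference halved to 5 as well

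*Protocol*

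**What the plan says.** Section 9.2 states every input to the calculation. The method is given as "Scenario: two sample T-test assuming equal variance", with "Target power – 80%. Alpha – 0.05. Proportion of subjects in groups – 1:1". Section 9.3 settles the sidedness: "The two-sided significance level of 0.05 (5%) will be applied for all statistical tests". The effect is a "clinically meaningful difference of -10 in the mean changes in complex attention". For the variability, "An estimate of 20 was obtained from the BRAINS pilot study (21) for standard deviation of change". The result is that "128 subjects (64 per arm) are required", raised to 182 randomised to allow for 30% dropout.

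Two numbered sensitivity checks follow. The first varies the difference and gives 29% power at 5 points and 99% at 20. The second varies the SD: "power is equal 15% if the standard deviation increases up to 30". From this the section concludes that uncertainty in the SD may leave the actual power too low.

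**The concern.** The two checks are numbered separately. The first names the differences it uses. The second names only an SD, so it should be read with everything else at its design value, including the difference of 10.

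On that reading the fall looks too steep. Moving the SD from 20 to 30 reduces the standardised difference from 10/20 = 0.50 to 10/30 = 0.33. Halving the difference at SD 20 reduces it further, to 5/20 = 0.25, and the protocol itself gives 29% for that harsher case. At a fixed sample size a standardised difference of 0.33 cannot have less power than one of 0.25. So 15% conflicts with the 29% in the same sentence before anything is recalculated.

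At stake is the accuracy of the only figure in the protocol that shows how power responds to the SD. The amendment table in section 18 records that this text was added when the health ministry asked about the sample size justification, so it is a figure that was put in front of a regulator.

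**Working it through.** **Inputs**, all from sections 9.2 and 9.3: n = 64 per arm, 1:1, two-sided alpha 0.05, equal-variance two-sample t-test, design difference d = 10 in absolute value, base SD s = 20, alternative SD 30.

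**Formula.** The standard error of the difference is s × √(2/n), and the noncentrality is d divided by it. Power is the probability that a noncentral t variable with 64 + 64 − 2 = 126 degrees of freedom falls beyond the two-sided 5% critical values. As a hand check, power ≈ Φ(noncentrality − 1.96).

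√(2/64) = 0.1768, so the standard error is 20 × 0.1768 = 3.536 at SD 20 and 30 × 0.1768 = 5.303 at SD 30.

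**Reproducing the protocol's figures, then the disputed one:**

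| Difference | SD | Noncentrality | Normal check | t-test power | Protocol |
|---|---|---|---|---|---|
| 10 | 20 | 10/3.536 = 2.828 | Φ(0.868) = 80.7% | 80.2% | 80% |
| 5 | 20 | 5/3.536 = 1.414 | Φ(−0.546) = 29.3% | 28.9% | 29% |
| 20 | 20 | 20/3.536 = 5.657 | above 99.9% | above 99.9% | 99% |
| 10 | 30 | 10/5.303 = 1.886 | Φ(−0.074) = 47.0% | **46.5%** | **15%** |
| 5 | 30 | 5/5.303 = 0.943 | Φ(−1.017) = 15.5% | 15.5% | not given |

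Solving the t-test for 80% power at d = 10 and s = 20 gives 63.8, hence 64 per arm, which is the protocol's 128. Allowing for dropout, 128/0.70 = 182.9; the planned 182 is within one patient of this, and nothing here depends on it.

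**Could another convention give 15% at a difference of 10 and SD 30?** The variants tried do not:

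- one-sided 5%, 64 per arm: 59.1%
- two-sided 2.5%, 64 per arm: 35.4%
- two-sided 5%, 32 per arm: 25.9%
- two-sided 5%, all 91 randomised per arm: 60.9%

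Section 9.2 writes its hypotheses in one direction, but a one-sided 5% test would give 87.9% in the base case, not 80%. The protocol's own numbers therefore confirm that the two-sided level was used.

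**What would give 15%?** At d = 10 and 64 per arm, the SD would have to be about 61. At d = 10 and SD 30, there would have to be about 16 patients per arm. The match close to the stated inputs is d = 5 with SD 30, at 15.5%.

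**The case against.** The best defence is that 15% is a correct calculation with a condition left out. The value 5 is the first difference tried in check 1, and 5 with SD 30 gives 15.5%. It is likely that the 5 was carried over, although this is an inference and only the sponsor can confirm it. It explains the number but does not rescue the sentence, which attributes the whole fall to the SD and draws a conclusion about the SD from it. It does bear on the repair: the sponsor must say which case was meant.

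Several other objections stand, and they limit the point:

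- A reader might infer that the section's conclusion on the SD fails along with the figure. It does not. The section does not claim to be robust; it warns that power may be insufficient, and 46% against a target of 80% bears that out.
- A reader might infer that the sample size is wrong. It was set at SD 20, and that calculation reproduces. The error understates power, so it does not flatter the design.
- A reader might fear a wrong decision on re-estimating or abandoning the trial. No rule in the protocol uses this figure: sections 4.5 and 9.4 contain no power-based stopping rule, no sample size re-estimation is planned, and under sections 8.5 and 11.6 the DSMB reviews blinded safety data.
- Section 9.2 also says "These results suggest that a difference in complex attention score in the range of 8-10 is clinically important", and a reader might count the lack of a check at 8 points as a second error. It is not one. The synopsis sets -10 as the minimally meaningful difference, and the 5-point check (29%) is already harsher than 8 points at SD 20 would be (61%).

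**Conclusion.** The stated 15% is wrong as written. At the design difference of 10, with 64 per arm and a two-sided 5% t-test, power at SD 30 is 46.5% (47.0% by the normal approximation). Measured as power lost, the protocol implies a drop from 80% to 15%, or 65 percentage points; the actual drop is from 80.2% to 46.5%, or about 34 points.

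This rests on reading check 2 as changing the SD alone, which is what its wording says, and on the protocol's planning method. It does not concern the mixed model that will be used for the primary analysis. The correction is confined to one figure: 128, 182, 80%, 29% and 99% stand, and so does the warning about the SD. For scale, 80% power at SD 30 would need about 143 evaluable patients per arm, so a larger SD remains a real risk to the trial.

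**What to change.** Amend the second sensitivity check in section 9.2 in one of two ways, after the sponsor has confirmed from the software output which case was run:

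1. replace 15% with about 46%, stating that it applies to a difference of 10 with SD 30 and 64 per arm; or
2. keep 15%, state that it applies to a difference of 5 with SD 30, and add 46% for a difference of 10 with SD 30.

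The synopsis does not repeat the figure, and the entry in the amendment table is a record of a past change, so neither needs editing. The edit is one sentence, with no change to the sample size, endpoints, analysis or conduct. Because section 11.4 sends protocol revisions to the ethics committees, it is sensible to include it in the next amendment rather than raise one for this alone.

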### **9.3 Level of Significance to be Used**

The two-sided significance level of 0.05 (5%) will be applied for all statistical tests.

### **9.4 Criteria for the Termination of the Study**

The sponsor may temporarily or permanently stop the study at one or all sites for safety, ethical, protocol compliance or other reasons. If such a need arises, the Sponsor will take steps to notify the center in advance. If a center or study is temporarily or permanently closed, the Investigator must promptly inform the local Ethics Committee. The Sponsor must promptly inform the regulatory authorities of the temporary or permanent closure of the center.

### **9.5 Procedure for Accounting for Missing, Unused, and Spurious Data**

No missing data will be substituted for primary analysis. LOCF imputation method will be employed for sensitivity analysis. Ambiguous data will be clarified via queries.

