## 2 BACKGROUND INFORMATION

### 2.1 Rationale

Traumatic brain injury (TBI) is a leading cause of disability and death in young adults globally (1-3). It was estimated that about half of the population has suffered from a TBI at some moment in their life (around 90% of all TBI cases are mild TBI), there are about 50 million people experiencing new TBI annually and the burden of TBI is increasing globally (1,4). The annual global cost of TBI is already immense and estimated to be around 400 billion US dollars (1).

Injury to the brain is caused from the mechanical impact of the brain onto the bony surfaces within the skull or from penetration of objects into the skull; and diffuse axonal injury (DAI) as a result of rotational forces as the brain moves within the skull. As a result of injury brain cells can die, affecting the functioning of areas that they help to control e.g. causing neurological/cognitive deficits. The most frequent sites of cerebral contusion in closed TBI are the temporal and basal-frontal regions, both of which are associated with cognitive functioning (5,6).

Persistent cognitive deficits have been reported to occur in up to half of adults following a mild TBI and can profoundly impact a person's day-to-day functioning, often affecting their ability to return to work, or impacting their capacity to engage in independent living (6,7). The most common cognitive deficits include difficulties with complex attention, executive functioning, cognitive flexibility and memory. After a brain injury (particularly for mild injuries) many people recover spontaneously as the brain mobilises surviving elements of the central nervous system in the damaged area to facilitate recovery (8). However often this spontaneous recovery process is insufficient, and people continue to experience cognitive, emotional and physical impairments (9-11).

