#### 9.1.2 Efficacy analysis

Primary analysis will employ ITT population, sensitivity analyses will be performed using ITT population with LOCF imputations and PP population.

Primary efficacy endpoint: Change in complex attention score, determined using Central Nervous System Vital Signs (CNS-VS) computer cognitive testing system, after 6 months of treatment compared to baseline in the group of patients receiving NeuroAiD II™ (MLC901), compared to the placebo group.

For primary endpoint analysis for each patient, the difference in complex attention scores, determined using CNS-VS computer testing, after 6 months of therapy compared to baseline, will be calculated: the change in complex attention score compared to baseline. Mixed effects model (PROC MIXED) will be used with adjustments for baseline and potential covariates. All timepoints will be used for the model. The participant and site will be used as the random effects. Model selection will be undertaken with each outcome using standard selection heuristics. Covariates will be selected based on improving the overall efficiency of the model. Regardless, baseline and age, gender, time since injury (1-3 months/4-12 months) and study center will be included as covariates in the mixed effects model. Descriptive statistics will be calculated to change in complex attention in each group, as well as mean values obtained by the method of least squares from the mixed effects model.

Superiority of MLC901 over placebo will be claimed if

$H_0: \text{LSM}_T \geq \text{LSM}_R$  is rejected and thereafter

$H_1: \text{LSM}_T < \text{LSM}_R$  is accepted at significance level of 5%,

where  $\text{LSM}_T$  is a Least Square Mean of Change from Baseline of Complex attention score after 6 months of treatment assessed by the mixed model repeated measures analysis in the MLC901 group and  $\text{LSM}_R$  is a Least Square Mean of Change from Baseline of Complex attention score

after 6 months of treatment assessed by the mixed model repeated measures analysis in the Placebo group (lower score of Complex attention is better).

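### LOCF is the only planned check that treats missing values differently, and it cannot show how far the primary result depends on missing at random

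*Protocol*

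**What the plan says.** Section 9.1.2 and the Synopsis (statistical methods) base the superiority claim on a mixed model in the ITT population, fitted to all timepoints. Section 9.5 adds that nothing is imputed for that analysis.

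Two sensitivity analyses are named in Section 9.1.2: "sensitivity analyses will be performed using ITT population with LOCF imputations and PP population". Section 9.5 repeats the first: "LOCF imputation method will be employed for sensitivity analysis". The Synopsis says the same as Section 9.1.2. Under Section 9.7 the PP population keeps ITT patients who completed the assessments needed for the primary endpoint and had no significant protocol deviation.

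Section 9.2 provides for substantial loss: "The sample size is increased to 182 randomized subjects (91 per arm) to allow for 30% dropouts". Section 2.1 says of brain injury, particularly mild injury, that "many people recover spontaneously", and then adds that this recovery is often not enough.

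**The concern.** A likelihood-based mixed model without imputation gives a valid month-6 comparison if, given the observed data, dropouts would have continued like comparable patients who stayed. With up to 30% of month-6 values possibly absent, a reader will want to know how strongly the result depends on that assumption, and a sensitivity analysis should answer this.

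Neither planned analysis does. PP removes patients without the endpoint. LOCF replaces one untestable assumption with another, namely that a score stays where it was at the last visit. It also enters the carried-forward value as if it had been observed at month 6. If LOCF agrees with the primary result, that does not establish robustness to departures from missing at random. If it disagrees, the cause may simply be that an effect still building was cut off early. A true finding could look fragile, or a fragile one sound, for reasons unrelated to the assumption under test.

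**Working it through.** **Step 1: the plan's own figures.** Inputs from Sections 9.2 and 9.3: difference 10, SD of change 20, power 80%, two-sided alpha 0.05, 1:1 allocation.
- Normal approximation: n per arm = 2 × (1.960 + 0.842)² × 20² / 10² = 62.8, so 63. The two-sample t-test named in the protocol needs 64 per arm (power 80.1%), which is the stated 128.
- Dropout: 128 / 0.70 = 182.9, against 182 stated. This agrees to within rounding.
- The allowance corresponds to 0.30 × 182 = 54.6, about 55 missing month-6 values.

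**Step 2: what LOCF estimates.** Benefit is counted as positive. Assumptions, not in the protocol: mean change is linear over 6 months, and dropouts were last seen at months 1 and 3 in equal numbers. The average dropout then shows (1/6 + 3/6) / 2 = 1/3 of the month-6 change. Let E be the true month-6 difference, R the mean placebo change, and dT and dP the dropout on drug and placebo:

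LOCF difference = (R + E)(1 − 2dT/3) − R(1 − 2dP/3) = E(1 − 2dT/3) + (2/3)R(dP − dT)

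| E | dT / dP | R | LOCF difference |
|---|---|---|---|
| 10 | 30% / 30% | any | 10 × 0.800 = 8.0 |
| 10 | 40% / 20% | 0 | 10 × 0.733 = 7.3 |
| 0 | 30% / 30% | any | 0 |
| 0 | 20% / 40% | −3.12 | −3.12 × 0.133 = −0.4 |
| 0 | 20% / 40% | 5 | 5 × 0.133 = +0.7 |
| 0 | 20% / 40% | 15 | 15 × 0.133 = +2.0 |

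R = −3.12 is the pilot placebo change in Table 9.1 (82.31 − 85.43). The values 5 and 15 are assumptions.

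**Step 3: sensitivity to the timing of dropout.** With 30% in both arms and E = 10, LOCF gives 7.0 if every dropout was last seen at baseline. It gives 7.7 if last visits are spread evenly over baseline, month 1 and month 3, and 8.5 if all were last seen at month 3. None of these depends on R. They depend only on the effect building up over time.

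**Step 4: false-positive rate of the LOCF comparison.** Simulated with 91 per arm and 4,000 trials per case. Variance components are subject SD 13, slope SD 8 at month 6 and residual SD 13 (√(169 + 64 + 169) ≈ 20), with no drug effect.
- 20% drug / 40% placebo dropout: rejection is 6.0% at R = −3.12, 5.4% at R = 5 and about 10% at R = 15.
- Equal 30% dropout with R = 15: rejection is 5.3%.

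**Step 5: what a delta adjustment would report.** Illustration: an estimate of 10, 30% of drug-arm values missing, and the SE held at 20 × √(2/64) = 3.54. The estimate must exceed 1.96 × 3.54 = 6.93. If missing drug-arm patients did delta points worse than assumed, the estimate becomes 10 − 0.3 × delta. Significance is lost at delta = (10 − 6.93) / 0.3 = 10.2, and the effect reaches zero at 10 / 0.3 = 33.3. LOCF supplies neither number.

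**The case against.** LOCF decides nothing in this trial. Superiority is claimed from the mixed model alone, and in the scenarios above dropout differs by arm but not by outcome, so a correctly specified mixed model would remain valid. That stands. A reader might infer that the trial's conclusion is at risk, but the figures show only that a secondary check can mislead.

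A reader might also infer that LOCF is likely to create a false positive because these patients are recovering. The documents do not support that. Section 2.1 qualifies its own remark, patients are enrolled with persisting complaints 1 to 12 months after injury, and the pilot placebo mean fell from 85.43 to 82.31. A 15-point recovery would bring that baseline to 100.43, against the normal mean of 100.41 cited in Section 9.2. The 10% rejection rate needs that full normalisation on placebo and also twofold unequal dropout. An early effect that vanishes by month 6 would mislead LOCF too, but nothing in the protocol suggests one. With equal dropout LOCF shrinks a real effect, which is conservative. Entering carried values as observed did not by itself inflate error in the simulation (5.3%).

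The 30% is an allowance and not a forecast. Section 5.4 keeps patients who stop treatment in follow-up where possible. Section 4.1 gives early leavers a termination visit with the End-of-Study assessments, CNS-VS included. Both would lessen the distortion, and the scenarios above leave out the termination visit.

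Finally, Section 9.1 defers detail to a statistical analysis plan, which is not at hand, and Section 9.6 lets methods be replaced. But the protocol names LOCF in three places, so this is a stated choice and not a detail left open. What remains after all this is that no stated analysis varies the missing-at-random assumption.

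**Conclusion.** The concern holds in a limited form. LOCF is not the only sensitivity analysis, since PP is named too, but it is the only one that handles missing values differently from the primary model. It does not test the assumption that the primary model makes. Under linear change and dropout after months 1 and 3, it turns a true 10 into about 8.0 with 30% dropout in both arms (7.0 to 8.5 across the timings tried). With 40% drug and 20% placebo dropout and no recovery it gives about 7.3. With no effect it is unbiased under equal dropout. With 20% drug and 40% placebo dropout it is off by −0.4 at the pilot placebo change and +0.7 at 5 points of recovery, rising to +2.0 only in the extreme 15-point case. The primary decision and the sample size are unaffected. The weakness lies in the evidence that the result is robust, so the change is advisable but not critical.

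**What to change.** In the Synopsis, Section 9.1.2 and Section 9.5, name a delta-adjusted multiple-imputation analysis with a tipping point as the main missing-data sensitivity analysis. Run it on the ITT population with the primary model. Fix the range of deltas and the arm or arms to which they apply before unblinding, and report the delta at which significance is lost. Reference-based imputation is optional, because it presupposes a view of what happens after treatment stops that the protocol would first have to state. LOCF may remain as a supplementary analysis, and PP as a supportive one.

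No new data and no change in sample size are needed. The cost is a little more programming, and the reported robustness may look less favourable than LOCF would have made it.
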